### 2.3. Study Population

Participants must fulfill all of the following inclusion criteria to qualify for study enrollment: (1) male and female between the age of 19 and 70; (2) radiographically diagnosed with ONFH; (3) ARCO stage 1 or 2 of the classification criteria for ONFH; (4) symptoms persistent after conservative treatment including medication with duration of at least 3 months; and (5) have voluntarily consented to participate in this clinical trial. Exclusion criteria are as follows: (1) a person with femoral head collapse due to rapidly progressing ONFH; (2) clinically significant abnormal values in a screening test (aspartate aminotransferase (AST) or alanine transaminase (ALT) levels are 2.5 times or more of the upper normal limit specified by the clinical laboratory); (3) malignant bone tumor or bone metastasis in the proximal femur; (4) previous history of malignant tumors (but can be included if there was no relapse within 5 years after completing a treatment); (5) diagnosed with inflammatory arthritis around the femoral head; (6) diagnosed with acetabular dysplasia with a lateral center-edge angle <20°; (7) post-traumatic ONFH; (8) systemic or local infectious disease requiring systemic antibiotic treatment; (9) diagnosed with human immunodeficiency virus (HIV), hepatitis infection; (10) requires continuous, systemic, and high-dose corticosteroid therapy (prednisone administration at 7.5 mg/day or more) or administration of immunosuppressant within 6 months after core decompression; (11) stem-cell therapy for ONFH before screening; (12) heavy alcoholism and overconsumption within 6 months of screening; (13) have undergone core decompression or other treatments or procedures that can affect the femoral head; (14) body mass index ≥ 40 kg/m^2^ at the screening visit; (15) females with a possibility of pregnancy and do not agree to use medically approved contraceptive methods during the study period; (16) pregnant or breastfeeding; (17) received an investigational new drug from another clinical trial within 4 months before participating in this study; and (18) when the investigator determines that the subject is not suitable to participate in this clinical trial.

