### 2.5. Procedure

Core decompression restores normal blood circulation within the femoral head by drilling a tunnel at the site of necrosis [6]. It reduces the increased intramedullary pressure and pain by promoting revascularization within the necrotic site [9]. In this clinical trial, a competent researcher or a designated physician will perform core decompression and administer CF-M801 through the following steps.

First, the size and location of the lesion will be checked before the procedure, and the patient will be placed on the fracture table. Then, a lateral small incision will be made, and a guide pin will be inserted for a core tract under fluoroscopic guidance (Figure 1). Next, an entry hole will be created using a cannulated solid reamer along the pin to guide a following hollow reamer, and an autogenous bone chip (which will be inserted distal to a mixture of hUC-Os) will be collected (Figure 2). Then, a core tract will be created using a hollow biopsy cannula with a diameter of 8–10 mm along the entry hole reaching to necrotic lesion, and a cylindrical autogenous bone block (which will be inserted as a bone plug following inserting autogenous bone chip) will be collected (Figure 3). Curettage will be performed to remove the necrotic bone, and the necrotic bone debris will be washed (Figure 4). During preparation of the recipient site, CF-M801 will be attached with collagen putty using fibrin glue. Collagen putty contains hydroxyapatite (HA) and tri-calcium phosphate (TCP) and can be identified under the fluoroscopic guidance. After the mixture of cell and collagen putty is brought to the necrotic lesion carefully under the fluoroscopic guidance, the remaining space in the core tract will be filled distally with the autogenous bone chip and cylindrical bone block collected in the previous steps. If there is significant space remaining in the distal portion of the core tract, a cylindrical HA and TCP block may be inserted (Figure 5). Gradual partial weight-bearing will be started at 6 weeks, and full weight-bearing walking will be permitted at 3 months postoperatively.

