### 2.6. Timeline and Study Protocol

After a volunteer provides written consent to participate in the clinical trial, necessary examinations and tests will be performed within 3 weeks before CF-M801 administration (Visit 1) according to the study protocol (Table 2). Participants who meet the inclusion/exclusion criteria in the eligibility assessment will be subjected to core decompression and CF-M801 administration (Visit 2). Participants will be checked for acute adverse events for 3 days after administration of CF-M801 and will visit the facility after 2 (Visit 3), 6 (Visit 4), and 12 (Visit 5) weeks for a safety assessment. The safety assessment will be performed based on the same schedule for all participants, with only the administration dose varying.

To determine the maximal tolerated dose (MTD) of CF-M801, three participants will be sequentially allocated to a group starting with the low-dose group (1 × 10^7^ cells) according to the standard 3 + 3 dose escalation scheme [29]. The first participants in each dose group will be monitored for acute adverse events including DLT for 3 days after CF-M801 administration. DLT refers to when adverse events related to CF-M801 with grade ≥3 are observed based on the definition from the National Cancer Institute—Common Toxicity Criteria (NCI-CTC) version 5.0 [30]. Another two participants will be assigned to the group when DLT does not occur. Up to 18 patients can be enrolled, depending on the development of DLT. The decision process is as follows: (1) If none of the three participants experiences DLT, the dose will be increased to the next level. (2) If one of the three participants experiences DLT, three participants will be additionally assigned to the same dose group. (3) If one of the six participants (initial three + additional three participants) experience DLT, the dose will be increased to the next level. (4) However, if at least two of the six participants experience DLT, dose escalation will be canceled, and the MTD will become the previous dose level. (5) If at least two of the three participants experience DLT, dose escalation will be canceled, and the MTD will become the previous dose level. (6) If one of the three additional participants show DLT, no additional participants will be assigned to the dose group, and current participants will be monitored for safety.

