**Figure 5 pharmaceuticals-17-01366-f005:**
[figure not shown]
A mixture of cell and collagen putty is implanted into the lesion (black arrow), and the autogenous bone chip and cylindrical bone block is inserted into the remaining space in the core tract (white arrow). If there is significant space remaining in the distal portion of the core tract, a cylindrical hydroxyapatite and tri-calcium phosphate block may be inserted (arrowhead).

**Table 1 pharmaceuticals-17-01366-t001:** Gross characterization of the cell therapy.

	Hematopoietic		Mesenchymal		Osteoblast		Angiogenesis
Markers	CD31	CD45	CD73	CD105	RUNX2	COL1A	ANGPT-1
Expression	≤5%	≤5%	≥50%	≥50%	≥5 copies	≥3000 pg/mL	≥2000 pg/mL

**Table 2 pharmaceuticals-17-01366-t002:** Protocol and timeline for outcome assessments.

Period	Screening	Treatment ^(g)^	Follow-Up 1	Follow-Up 2	Study Completion /Dropout ^(i)^
Visit	1	2	3	4	5 ^(i)^
Week	Within-3	0	2	6	12
Visit window (days)	-	Within-3	±3	±7	+7
Written consent form ^(a)^	X				
Demographic information	X				
Body weight and height measurement	X				
Review medical/operation history	X	X ^(h)^			
Review medication history	X	X ^(h)^			
Vital signs ^(b)^	X	X ^(h)^	X	X	X
Physical examination	X	X ^(h)^	X	X	X
Clinical laboratory tests ^(c)^	X ^(C−1), C−2)^		X	X	X ^(C−1)^
ECG test	X		X	X	X
Pregnancy test ^(d)^	X				X
Radiographic examination	X ^(e)^		X	X	X
MRI examination	X				X
ARCO classification	X				X
JIC classification	X				X
Review inclusion/exclusion criteria	X	X			
Patient selection		X			
Group allocation		X			
Core decompression		X			
hUC-Os administration		X			
Pain VAS assessment		X ^(h)^			X
HHS assessment		X ^(h)^			X
WOMAC assessment		X ^(h)^			X
Adverse events assessment		X ^(f)^	X	X	X
Check concomitant drug use		X	X	X	X

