ECG, electrocardiogram; MRI, magnetic resonance imaging; ARCO, Association Research Circulation Osseous; JIC, Japanese Investigation Committee; hUC-Os, human umbilical cord-derived osteoblasts; VAS, visual analog scale; HHS, Harris hip score; WOMAC, Western Ontario and McMaster Universities. ^(a)^ Written consent can be obtained from participants before the screening visit. ^(b)^ For vital signs, pulse, blood pressure, and body temperature will be measured. At Visit 2, vital signs will be measured before hUC-O administration. ^(c)^ For screening tests, test results obtained within 4 weeks after a visit can be used. A retest may also be performed once at the discretion of a researcher during the screening period. The following parameters are assessed during the laboratory tests. Blood test: red blood cell (RBC) count, hemoglobin, hematocrit, platelet count, white blood cell (WBC) count, WBC differential count (neutrophil, lymphocyte, monocyte, eosinophil, and basophil), and erythrocyte sedimentation rate; Blood chemistry test: total protein, albumin, total bilirubin, aspartate aminotransferase or alanine transaminase, gamma-glutamyl transpeptidase, blood urea nitrogen, creatinine, glucose, alkaline phosphatase, total cholesterol, triglyceride, uric acid, C-reactive protein, panel reactive antibody ^(C−1)^, virus infection test (human immunodeficiency virus antigen/antibody, hepatitis B surface antibody, anti-hepatitis C virus antibody, venereal disease research laboratory) ^(C−2)^; Urinalysis: protein (albumin), glucose, ketones, WBC, RBC. ^(d)^ A serum or urine human chorionic gonadotropin test will be performed for women of childbearing age except for those who have been sterilized or are menopausal. Women of childbearing age refer to women who have had their first period, have not been successfully surgically sterilized (via hysterectomy, bilateral tubal ligation, or bilateral oophorectomy), and are not menopausal. Menopause is defined as not having a period for >12 months after the final menstrual period. ^(e)^ Test results obtained within 4 weeks after screening can be used. ^(f)^ Acute adverse events that occur within 3 days after hUC-O administration will be investigated. ^(g)^ Patients will be hospitalized starting 1 day before hUC-O administration and will be monitored throughout the hospitalization period for adverse events. ^(h)^ Performed within 3 days and restrict intake of analgesics within 1 day before hUC-O administration. ^(i)^ For participants who were withdrawn following the group allocation, the procedures scheduled for the last visit will be performed.

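### No pregnancy test is scheduled at Visit 2, so the pregnancy exclusion can rest on an hCG result up to 21 days old at surgery and cell implantation

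*Protocol article*

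**What the plan says.** Section 2.3 excludes anyone who is "16) pregnant or breastfeeding". Exclusion 15 in the same list removes "females with a possibility of pregnancy and do not agree to use medically approved contraceptive methods during the study period".

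Section 2.6 sets the timing of screening: "necessary examinations and tests will be performed within 3 weeks before CF-M801 administration (Visit 1").

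In Table 2 the row "Pregnancy test ^(d" carries a mark at Visit 1 (screening) and Visit 5 (Week 12), and none at Visits 2, 3 or 4. Footnote (d) defines the test and who receives it: "A serum or urine human chorionic gonadotropin test will be performed for women of childbearing age", apart from those who are sterilized or menopausal. It does not mention a repeat before dosing.

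The same table marks the eligibility review at both Visit 1 and Visit 2. Visit 2 also holds patient selection, group allocation, core decompression and cell administration. Several Visit 2 items (history, medication, vital signs, physical examination, pain VAS, HHS and WOMAC) carry footnote (h): "Performed within 3 days and restrict intake of analgesics within 1 day before hUC-O administration". The pregnancy test is not among them. Footnote (g) states: "Patients will be hospitalized starting 1 day before hUC-O administration".

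**The concern.** Visit 2 is the last point at which exclusion 16 can still prevent exposure. Eligibility is confirmed again there, but the only objective evidence on pregnancy comes from screening. A pregnancy that began after Visit 1, or too shortly before it to be detected, would pass the review.

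What follows is hip surgery in which "a guide pin will be inserted for a core tract under fluoroscopic guidance" (Section 2.5), then implantation of an allogeneic cell product that the Discussion presents as the first of its kind given directly into the lesion. After that, Table 2 schedules radiographs at Weeks 2 and 6 but no further hCG test until Week 12. A pregnancy missed at Visit 2 could therefore go unrecognised by the scheduled tests for most of the follow-up.

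The stake is the safety of the participant and the pregnancy. Dose escalation, determination of the MTD and the descriptive analysis are unaffected.

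**Working it through.** The plan states no figure for this interval, so there is none to reproduce. The check reads the schedule and then does simple arithmetic on it.

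**Inputs**

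- Pregnancy test at Visits 1 and 5 only (Table 2).
- Visit 1 up to 3 weeks before administration (Section 2.6; Table 2, week row).
- Eligibility review at Visits 1 and 2 (Table 2).
- Admission 1 day before administration (footnote (g)).
- Pre-dose window of 3 days for other Visit 2 items (footnote (h)).
- Period *w* after conception during which hCG can still be negative: not in the documents. Assumed range 7 to 14 days.

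**Are the table columns reliable after extraction?** Two rows can be checked against the text. Section 2.9 puts MRI at Visits 1 and 5, and Section 2.7.5 puts the ECG at Visits 1, 3, 4 and 5. Both match Table 2, so the pattern for the pregnancy row can be trusted.

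**Is 21 days the right bound?** Older results, up to 4 weeks, may be used for laboratory tests (Section 2.7.2, footnote (c)) and radiographs (footnote (e)). Neither allowance is attached to the pregnancy test, and hCG is not in the listed laboratory panel. The bound is therefore the screening window.

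**Gap from test to surgery**

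- As planned: 3 weeks × 7 = 21 days at most.
- With a test in the footnote (h) window: 3 days at most.
- With a test at admission: about 1 day.
- Reduction with the admission test: 21 − 1 = 20 days.

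**Longest window in which a conception before surgery goes undetected** (gap + *w*)

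| Assumed *w* | As planned | Test at admission | Reduction |
|---|---|---|---|
| 7 days | 21 + 7 = 28 days | 1 + 7 = 8 days | 20/28 = 71% |
| 14 days | 21 + 14 = 35 days | 1 + 14 = 15 days | 20/35 = 57% |

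These percentages describe the length of the longest window. They are not reductions in the probability of an exposed pregnancy, and a woman screened closer to surgery gains less.

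**Do the other checks close the gap?** Exclusion 15 secures an agreement to use contraception. It does not confirm adherence or success. The history and examination repeated within 3 days of dosing may bring a missed period to light, but they do not establish early pregnancy. What remains is contraceptive failure or non-adherence between Visits 1 and 2, and conception just before Visit 1.

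**The case against.** The strongest objection is that this is a condensed article and the schedule may not list every peri-operative check. Laboratory tests and the ECG are also unmarked at Visit 2, although patients are admitted the day before an operation, and a hospital may well test for pregnancy before surgery as routine. That is possible, but the article does not say so. It does print an explicit schedule with a dedicated row and footnote for this test, which is a positive statement of when the test is done. Eligibility should not depend on an unstated practice.

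A second objection is that nothing is contradicted. Reviewing criteria at Visit 2 does not promise that every screening test is repeated, and the liver-enzyme and infection exclusions also rest on screening results. This is fair: the point is a weak design choice and not an inconsistency.

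A third is that the risk is small. Contraception is required, the investigator may exclude anyone judged unsuitable (exclusion 18), and only 9 to 18 men and women aged 19 to 70 will be enrolled. This also stands. The documents give no sex distribution, so no absolute risk can be stated. Nor does the remedy remove the risk entirely, since a very early pregnancy could still be missed. These points limit the size of the concern but do not answer it, because none of the existing safeguards verifies pregnancy status at the point of exposure.

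**Conclusion.** The concern holds. As scheduled, exclusion 16 can be judged at Visit 2 on an hCG result up to 21 days old, immediately before surgery and implantation. That bound follows from the document alone and needs no outside assumption. The wider figures, 28–35 days now against 8–15 days with a test at admission, rest on the assumed 7 to 14 days of hCG negativity.

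The number of women exposed to this gap is unknown and probably small. The change is still worth making, because the possible harm is serious and the remedy costs almost nothing.

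**What to change.** In Table 2, add a mark for the pregnancy test at Visit 2, using the serum or urine hCG test already defined in footnote (d) and done at the admission described in footnote (g). Add to footnote (d): *At Visit 2 a negative result is required before core decompression.* Leave exclusion 15 and the Visit 2 history and examination as they are.

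The cost is one table mark, one sentence and one hCG test per woman of childbearing age. No visit is added.

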## 2. Methods

### 2.1. Aims of This Study

The purpose of this study is to evaluate the safety and exploratory efficacy of hUC-Os. This is a phase I clinical trial in which safety is the main concern and will be determined through adverse event assessment, laboratory tests, vital sign assessment, a physical examination, and an electrocardiogram (ECG) test. In addition, we aim to assess the exploratory efficacy of hUC-Os by comparing subjective preoperative and postoperative patient-reported outcomes, specifically, the pain visual analog scale (VAS) [20], Harris hip score (HHS) [21], and Western Ontario and McMaster Universities Osteoarthritis Index (WOMAC) [22]. Also, we aim to assess the radiographic results after hUC-O-based cell therapy using simple radiography and magnetic resonance imaging (MRI). The preoperative and postoperative the Association Research Circulation Osseous (ARCO) stage [23], necrotic lesion size [24,25], and Japanese Investigation Committee (JIC) stage [26] will be compared.

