### 2.8. Clinical Assessment

#### 2.8.1. Pain VAS Assessment [20]

Participants will mark their subjective pain level around the hip joint on a scale that ranges from “no pain (0)” to “severe pain (10)”. The examiner will determine the number corresponding to the point marked on the scale and record it to one out of 10 decimal places. To examine the changes in pain VAS at different time points after CF-M801 administration, pain VAS assessment will be performed at Visits 2 and 5.

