#### 2.8.2. HHS Assessment [21]

HHSs will be assessed at Visits 2 and 5 to examine the participants’ hip joint function. The highest possible score is 100, and the following domains will be assessed: pain (44 points), gait function (11 points), support devices (11 points), distance walked (11 points), stairs (4 points), putting on shoes (4 points), sitting (5 points), entering public transportation (1 point), presence of deformity (4 points), and hip joint range of motion (5 points).

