#### 2.8.3. WOMAC Score Assessment [22]

WOMAC scores will be assessed at Visits 2 and 5 to examine the changes in WOMAC scores after CF-M801 administration and assess participants’ joint function. WOMAC assesses three domains, namely, pain, stiffness, and physical function.

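### The analgesic restriction is attached to the Visit 2 VAS, HHS and WOMAC scores but not to the paired Visit 5 scores, so the exploratory pre-post change can compare unlike conditions

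*Protocol article*

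**What the plan says.** The exploratory efficacy aim in section 2.1 rests on "comparing subjective preoperative and postoperative patient-reported outcomes", namely the pain VAS, HHS and WOMAC. Each is scored twice. Section 2.8.1 states that "pain VAS assessment will be performed at Visits 2 and 5", section 2.8.2 that "HHSs will be assessed at Visits 2 and 5", and section 2.8.3 that "WOMAC scores will be assessed at Visits 2 and 5 to examine the changes in WOMAC scores after CF-M801 administration". None of the three sections mentions analgesics.

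The only analgesic restriction in the article is Table 2 footnote (h): "Performed within 3 days and restrict intake of analgesics within 1 day before hUC-O administration". In the rows for the three scales the mark (h) stands on the Visit 2 cell, while the Visit 5 cell is a plain X. The same mark also stands on the Visit 2 cells for medical and medication history, vital signs and physical examination.

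Two other entries bear on the point. The row "Check concomitant drug use" is marked at Visits 2 to 5. Footnote (g) says "Patients will be hospitalized starting 1 day before hUC-O administration".

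**The concern.** Each participant is his or her own comparator, and there is no untreated group in which a difference in measuring conditions would cancel. The pain VAS, the HHS pain domain (44 of 100 points) and the WOMAC pain domain can all respond to analgesics. If the baseline is taken off analgesics and the week-12 score on them, part of the apparent improvement is the drug.

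Analgesic use around the scores is plausible. Section 2.3 requires symptoms that persist despite at least 3 months of conservative treatment, medication included. The article does not say how many participants would be taking analgesics at week 12.

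At stake is the reading of three descriptive scales, not the trial's main objective.

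**Working it through.** The plan gives no figure to reproduce. The check sets the scoring times that Table 2 permits against the restriction in footnote (h).

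**Inputs**
- Visit 2 scores: within 3 days before dosing (Table 2, footnote (h)).
- Restriction: within 1 day before dosing (footnote (h)).
- Visit 5 scores: week 12, window +7 days, no footnote (Table 2).
- Analgesic condition in sections 2.8.1 to 2.8.3: none.
- Assumptions: 1 day is 24 h, 3 days are 72 h, and restricting intake means none is taken.

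**Direction of the bias**

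Take a scale on which lower is better, such as the VAS. Let B and F be the scores a participant would give without analgesics at Visit 2 and Visit 5. Let e2 and e5 (zero or more) be the reduction from any analgesic in effect at each score.

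Reported improvement = (B − e2) − (F − e5) = (B − F) + (e5 − e2).

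The error is e5 − e2. With a restricted baseline, e2 = 0 and the error is e5. That is zero if no analgesic precedes the Visit 5 score and otherwise inflates improvement. On the HHS, where higher is better, the signs flip and the conclusion is the same. With no restriction at either visit, the error e5 − e2 can go either way.

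**Reading 1: footnote (h) tied to dosing, as literally written**

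For a baseline scored t hours before dosing, the guaranteed analgesic-free time before the score is max(0, 24 − t).

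| t (hours before dosing) | Guaranteed at Visit 2 | Guaranteed at Visit 5 |
|---|---|---|
| 0 | 24 h | 0 h |
| 12 | 12 h | 0 h |
| 24 | 0 h | 0 h |
| 48 | 0 h | 0 h |
| 72 | 0 h | 0 h |

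A baseline in the last day is fully or partly restricted and its Visit 5 partner is not. A baseline on day -3 or -2 is unrestricted, as at Visit 5. The guaranteed gap between visits runs from 0 to 24 h, depending on when the baseline was scored, so it may differ between participants.

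**Reading 2: footnote (h) as an analgesic-free day before the Visit 2 score**

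Every baseline is then restricted for 24 h and no Visit 5 score is. Baselines are even across participants, but the mismatch between visits applies to all of them.

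**Result**

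On both readings the article permits a restricted baseline to be paired with an unrestricted week-12 score. The uneven baseline arises only on reading 1.

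**The case against.** **This is an article, and the full protocol may hold the rule.** That is a fair caution: a Visit 5 condition may exist there, and it would remove the main point. But the schedule is not silent. It states a restriction on one cell of each pair and leaves the other bare, which is more than condensed detail.

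**The footnote may be a pre-operative instruction, not a scoring rule.** It is shared with history, vital signs and examination, and it is tied to administration of the cells, which takes place at surgery. The article does not state its purpose, so a reader who infers that a scoring rule was forgotten at Visit 5 goes further than the text allows. The effect does not depend on intent: a score taken in the restricted day is restricted either way.

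**The uneven baseline depends on one reading of a loose sentence.** This stands. Admission is 1 day before dosing, and nothing shows that anyone will be scored earlier. It can only be claimed conditionally.

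**Drug use is already checked.** True, at Visits 2 to 5, so some of the difference will be visible. The check records use; it does not restrict it, and Table 2 does not tie it to the time of the score.

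**The scales carry little weight.** This stands too. Section 2.10.2 plans description only, and the Discussion concedes that 12 weeks cannot settle efficacy. Every participant also has core decompression, so change could not be credited to the cells alone. Section 2.5 allows full weight-bearing only at 3 months, close to Visit 5, so functional conditions differ anyway. These facts limit the importance of the point without removing it.

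**Conclusion.** The point holds in a limited form. As written, Table 2 restricts analgesics at the Visit 2 VAS, HHS and WOMAC scores only, so a restricted baseline can be compared with a week-12 score taken on analgesics. The error would favour apparent improvement.

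Its size is unknown and is zero for any participant with a restricted baseline who takes no analgesic before the Visit 5 score. The conclusion assumes that the restriction means no intake and that the full protocol sets no matching Visit 5 condition. If it does set one, only the possible unevenness at baseline remains, and that in turn requires the literal, dosing-anchored reading.

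Three stronger readings are not supported:
- A reader might infer that matched conditions are impossible. Nothing stops a participant from being analgesic-free at Visit 5; the article only fails to require it.
- A reader might infer that baselines will differ between participants. They may, on one reading of the footnote.
- A reader might put a number on the bias by dividing one participant's analgesic effect by the group size. That only rescales an effect for which the article gives no value.

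Minor. Only three descriptive, exploratory scales are touched; safety, DLT, MTD, MRI and staging readouts are unaffected.

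**What to change.** Give the three scales their own footnote, separate from (h), on both the Visit 2 and the Visit 5 cells. Suggested wording: *VAS, HHS and WOMAC: no analgesics in the 1 day before the assessment, at Visit 2 (within 3 days before hUC-O administration) and at Visit 5.* Anchoring the rule to the assessment matches the two visits and also settles the uneven-baseline question.

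Where withholding analgesics is clinically unacceptable, record use in the 24 h before each score within the existing concomitant drug check, and list it beside that participant's change.

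The cost is footnote wording plus either a short analgesic restriction before Visit 5 or one CRF item. This is a cheap improvement.
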